#### Relevant concomitant care permitted or prohibited during the trial {11d}

All medical or surgical treatments, besides the allocated BP management, are permitted during the study; they are to be recorded on the case report form (CRF).

#### Provisions for post-trial care {30}

Not applicable. This study is evaluating the effectiveness of intensive BP lowering commenced in the ambulance in patients with suspected hyperacute stroke. The result may modify current medical practice, in particular over pre-hospital assessment and care. However, as this intervention is already available in routine practice, it can be sustained beyond completion of the study.

### Outcomes {12}

The primary outcome is functional recovery on the modified Rankin scale (mRS) measured by structured interview at 3 months, with analysis as an ordinal outcome (shift across all seven scoring categories of physical function that range from 0 to 5, with death as 6) [14].

Secondary outcomes include:

• For ICH patients—hematoma volume at presentation and 24 h, with analysis as dichotomized outcomes of relative (> 33%) and absolute (> 6 mL) growth over 24 h

• For IS patients—time to, and rate of, reperfusion treatment (thrombolysis and/or thrombectomy); infarct size on MRI within 2 days after stroke onset; and frequency of symptomatic intracranial hemorrhage, measured centrally with standard definitions

• For all stroke patients—functional outcomes (death or dependency [mRS scores 3-6]) at 3 months; separately on death or dependency at 3 months; death or neurologic deficit progression measured by National Institutes of Health Stroke Scale (NIHSS) scores [15] at 24 h and 7 days, with analysis as a continuous outcome using linear regression with adjustment for baseline score; and length of hospital stay, place of residence, and health-related quality of life (HRQoL) according to the EuroQoL Group 5-Dimension self-report questionnaire (EQ-5D) [16], all at 3 months

Safety outcomes in all participants including those with a transient ischemic attack and stroke mimic will be recorded for the duration of follow-up. They will be assessed as all-cause and cause-specific SAEs and categorized according to standard organ system-specific criteria.

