### Participant timeline {13}

The schedule of randomization for sites as well as enrolment, treatment allocation, and assessments for participants is outlined in Table 1.

**Table 1 Tab1:** Collection of data in INTERACT4

Evaluation	Screen + enrolment log	Baseline	Day 1	7 days/discharge/transfer/death^**a**^	BP monitoring chart	3-month follow-up
Forms	A	B	C	D	E	F
Eligibility	X					
Consent/re-consent	X			X		
Vital signs	X	X	X	X		
BP	X^b^	X	X	X	X^c^	
GCS		X	X	X		
NIHSS		X	X	X		
Medical history		X				
CT scan		X	X	X		
MRI scan for AIS			X			
mRS		X		X		X
EQ-5D						X
Routine blood tests		X		X		
Standard stroke care		X		X		
Final diagnosis				X		
Medications in use			X	X		X
SAEs			X	X		X
Healthcare cost	X			X		X

*Abbreviations: AIS* acute ischemic stroke, *BP* blood pressure, *CT* computerized tomography, *EQ-5D* EuroQol 5 dimensions instrument for assessment of health-related quality of life, *GCS* Glasgow coma scale, *MRI* magnetic resonance imaging, *mRS* modified Rankin scale, *NIHSS* National Institute of Health stroke scale, *SAEs* serious adverse events

^a^Assessed at earliest time point among day 7, discharge, transfer, or death

^b^Q5 min for 30 min after randomization; Q15 for 1 h

^c^Q15 min for 1 h after admission to hospital; hourly from 1 to 6 h after admission to hospital; 6 hourly from 6 to 24 h after admission to hospital. At any point where intravenous bolus drugs are administered, BP and HR are recorded 5 and 15 min later, respectively

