### Sample size {14}

The sample size for this study is based on 90% power (*p* = 0.05) to detect a 22% reduction in the odds (common odds ratio [OR] of 0.78) of a worse outcome using an ordinal logistic regression. Assuming a distribution of mRS in the control group that is similar to that observed in the placebo group of the Field Administration of Stroke Therapy–Magnesium (FAST-MAG) trial [17], the largest pre-hospital stroke management trial that included suspected stroke patients within 2 h of symptoms onset (mRS distribution of 18.4%, 16.2%, 18.3%, 13.3%, 10.6%, 10.2%, and 13.0%, for scores of 0 to 6, respectively), it would correspond to a 6.1% absolute improvement in the proportion of patients experiencing a poor outcome (mRS scores 3-6), that is from 47.1% down to 41.0%. This would translate into a 13% relative risk reduction (relative risk of 0.87). Assuming 30% of participating patients will have a stroke mimic and 5% will have missing outcomes, the total sample size is 3116 participants to be recruited over 3 years.

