Binary endpoints such as death and dependency and early neurological deterioration will be analyzed using adjusted binary logistic regression. Continuous outcomes, such as NIHSS score or changes in hematoma volume, will be analyzed using linear regression that includes the baseline outcome value (e.g. NIHSS score or hematoma volume) as a covariate.

A detailed analysis plan including mock tables will be finalized before the database is locked.

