### Methods in analysis to handle protocol non-adherence and any statistical methods to handle missing data {20c}

The ITT approach is to be performed as the primary analysis of intervention effect. A sensitivity analysis or per-protocol approach will be conducted to detect the consistency of primary outcome. The population involved in the final analysis will be fully described, and the differences of baseline characteristics between analyzed and enrolled populations will be compared. Any missing primary outcomes at 90 days will be handled using a multi-imputation method incorporating each patient’s baseline variables, and all available neurologic deficits (NIHSS) and global disability (mRS) values.

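### A death-or-progression composite is assigned to linear regression of the NIHSS, a model that does not fit it and gives deaths no place

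*Protocol article*

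**What the plan says.** In the protocol article, Outcomes {12} lists for all stroke patients "death or neurologic deficit progression measured by National Institutes of Health Stroke Scale (NIHSS) scores", to be assessed "at 24 h and 7 days, with analysis as a continuous outcome using linear regression with adjustment for baseline score". The same section gives death an explicit place in the primary mRS outcome: "shift across all seven scoring categories of physical function that range from 0 to 5, with death as 6". No such value is given for the NIHSS.

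Statistical methods {20a} has two relevant sentences:

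- "Binary endpoints such as death and dependency and early neurological deterioration will be analyzed using adjusted binary logistic regression".
- Directly after it: "Continuous outcomes, such as NIHSS score or changes in hematoma volume, will be analyzed using linear regression", with the baseline value as a covariate.

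Table 1 schedules the NIHSS on the shared form for day 7, discharge, transfer or death, with the footnote "Assessed at earliest time point among day 7, discharge, transfer, or death". The missing-data rule in {20c} reads: "Any missing primary outcomes at 90 days will be handled using a multi-imputation method". It draws on available NIHSS values as predictors and does not supply NIHSS values for patients without one.

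**The concern.** Death or progression is an event: a patient either has it or does not. A baseline-adjusted linear regression estimates a difference in mean score among patients who have a score. The two do not correspond, and patients who died, who most clearly have the event, have no value to enter.

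If deaths fall out of the model, the arms are compared among survivors only. An arm that keeps severely ill patients alive then carries their high scores in its mean, while an arm with more early deaths loses its worst patients from the comparison. The death half of the composite would be lost, and the direction of the result could be set by a choice that the article does not state.

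The statistics section adds uncertainty. It places early neurological deterioration under logistic regression, and Outcomes {12} lists no deterioration endpoint other than this composite.

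**Working it through.** **The plan's own figure.** The article states no number for the NIHSS outcome. Its sample size is for the mRS: "to detect a 22% reduction in the odds (common odds ratio [OR] of 0.78) of a worse outcome using an ordinal logistic regression", with 90% power and 3116 patients. The Whitehead proportional-odds formula (1:1, two-sided 0.05) gives

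N = 12(1.960 + 1.282)² / [ln(0.78)² × (1 − Σp̄³)] ≈ 2096 evaluable,

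and 2096 / (0.70 × 0.95) ≈ 3151, within about 1% of 3116. The stated total therefore reproduces. It implies 3116 × 0.70 × 0.95 = 2072 evaluable stroke patients (1036 per arm), used below only to set the scale.

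**Does the stated model fit the named outcome?**

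| Item | Outcomes {12} | Statistical methods {20a} |
|---|---|---|
| Death or progression composite | Linear regression, baseline-adjusted | Not named |
| Early neurological deterioration | Not listed under that name | Logistic regression |
| NIHSS score | Linear regression (within the composite) | Linear regression, baseline-adjusted |
| Value for death | mRS: 6; NIHSS: none | None |

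The sections agree on the raw score. The composite itself is given only a model for the raw score.

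**Illustration of what hangs on deaths.** None of these inputs is in the article; all are assumed: 7-day mortality 6% in arm A and 4% in arm B; mean NIHSS 8 among the 94% who survive in either arm; NIHSS 20 for the 2% saved in B; SD 5 among survivors; 1036 per arm.

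*Deaths excluded*
- A: 8.00
- B: (0.94 × 8 + 0.02 × 20) / 0.96 = 7.92 / 0.96 = 8.25
- B − A = +0.25; SE = 2 × 5 / √2072 = 0.22; ratio about 1.1

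*Death scored 42*
- A: 0.94 × 8 + 0.06 × 42 = 10.04
- B: 0.94 × 8 + 0.02 × 20 + 0.04 × 42 = 9.60
- B − A = −0.44
- The SDs rise to about 9.4 (A) and 8.4 (B), so SE = √((9.4² + 8.4²) / 1036) ≈ 0.39; ratio about 1.1

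In general, with mortality gap g and saved patients at score s, the contrast is g(s − 8)/(1 − B's mortality) with deaths excluded and −g(42 − s) with death scored 42. The signs are opposite for any s between 8 and 42, and both contrasts are zero when g = 0.

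**Range.** A simulation on other assumed inputs (mean baseline NIHSS about 9, deaths concentrated in the most severe patients, no treatment effect on the NIHSS itself) gave, for intensive minus control:

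| 7-day mortality, control vs intensive | Deaths excluded | Death scored 42 |
|---|---|---|
| 3% vs 3% | 0 | 0 |
| 5% vs 3% | +0.31 | −0.41 |
| 3% vs 5% | −0.31 | +0.41 |
| 8% vs 5% | +0.40 | −0.69 |

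**The case against.** **The two sections contradict each other.** A reader might infer this from the logistic sentence in {20a}. The sentence after it assigns the NIHSS score to baseline-adjusted linear regression, as Outcomes {12} does. There is a direct contradiction only if early neurological deterioration is the Outcomes {12} composite. That is likely, since no other deterioration endpoint is listed, but it is nowhere stated. What stands is a need to reconcile the sections.

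**The plan excludes deaths.** The article does not say so. Naming death in the outcome could equally point to a worst-score rule. The Table 1 footnote dates a shared form and does not say that an NIHSS is scored for a patient who has died. A death score or a progression cut-off may properly be left to the SAP, and its absence alone is no finding. The misfit remains, because the article itself fixes the type of analysis.

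**The effect is about three standard errors.** One could divide the full swing (0.25 + 0.44 = 0.69) by 0.22. That mixes a swing between two analyses with the SE of only one of them. Scoring deaths 42 raises the SE to about 0.39, and each contrast is then about 1.1 SE. The 0.25 is also an unadjusted difference. Adjustment for baseline NIHSS would absorb part of it.

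**Mortality is counted elsewhere.** This is correct: in the primary mRS, in death or dependency, in death at 3 months, and among the serious adverse events. Section {20a} also calls the secondary analyses hypothesis-generating. This limits the consequence but does not make the model suit the outcome.

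**Conclusion.** The point holds as a misfit between a named secondary outcome and the analysis fixed for it. As written, the regression either omits deaths or does not estimate the composite, and neither a death score nor the imputation rule in {20c} repairs this.

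On the assumed inputs, the choice moves the contrast from 0.25 points against the lower-mortality arm to 0.44 points in its favour, each about 1.1 SE. The robust part is the reversal of sign when early mortality differs. The size depends on the assumed mortality gap and on the scores of the saved patients, and there is no effect if mortality is equal. The documents support neither a proven contradiction between sections nor a stated exclusion of deaths. The wording should be corrected, but the primary analysis and the sample size of 3116 do not depend on it.

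**What to change.** Split the item in Outcomes {12} into two:

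- (a) A binary endpoint: death, or an NIHSS increase of at least a prespecified amount, by 24 h and by 7 days, analysed with the adjusted logistic model of {20a}.
- (b) The NIHSS score at 24 h and 7 days, with deaths included as the worst rank in an ordinal or rank-based analysis adjusted for baseline score. The linear regression among survivors is kept as supportive and labelled as such.

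Remove the linear-regression clause from the composite. In {20a}, use the same endpoint names, state whether early neurological deterioration is endpoint (a), and bring the sentence on the NIHSS score into line with (b).

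The cost is wording and a little extra analysis. No additional data or patients are needed, and the article says that the detailed analysis plan is to be finalised before database lock, which leaves a place to record the change.

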### Participant timeline {13}

The schedule of randomization for sites as well as enrolment, treatment allocation, and assessments for participants is outlined in Table 1.

**Table 1 Tab1:** Collection of data in INTERACT4

Evaluation	Screen + enrolment log	Baseline	Day 1	7 days/discharge/transfer/death^**a**^	BP monitoring chart	3-month follow-up
Forms	A	B	C	D	E	F
Eligibility	X					
Consent/re-consent	X			X		
Vital signs	X	X	X	X		
BP	X^b^	X	X	X	X^c^	
GCS		X	X	X		
NIHSS		X	X	X		
Medical history		X				
CT scan		X	X	X		
MRI scan for AIS			X			
mRS		X		X		X
EQ-5D						X
Routine blood tests		X		X		
Standard stroke care		X		X		
Final diagnosis				X		
Medications in use			X	X		X
SAEs			X	X		X
Healthcare cost	X			X		X

*Abbreviations: AIS* acute ischemic stroke, *BP* blood pressure, *CT* computerized tomography, *EQ-5D* EuroQol 5 dimensions instrument for assessment of health-related quality of life, *GCS* Glasgow coma scale, *MRI* magnetic resonance imaging, *mRS* modified Rankin scale, *NIHSS* National Institute of Health stroke scale, *SAEs* serious adverse events

^a^Assessed at earliest time point among day 7, discharge, transfer, or death

^b^Q5 min for 30 min after randomization; Q15 for 1 h

^c^Q15 min for 1 h after admission to hospital; hourly from 1 to 6 h after admission to hospital; 6 hourly from 6 to 24 h after admission to hospital. At any point where intravenous bolus drugs are administered, BP and HR are recorded 5 and 15 min later, respectively

### Sample size {14}

The sample size for this study is based on 90% power (*p* = 0.05) to detect a 22% reduction in the odds (common odds ratio [OR] of 0.78) of a worse outcome using an ordinal logistic regression. Assuming a distribution of mRS in the control group that is similar to that observed in the placebo group of the Field Administration of Stroke Therapy–Magnesium (FAST-MAG) trial [17], the largest pre-hospital stroke management trial that included suspected stroke patients within 2 h of symptoms onset (mRS distribution of 18.4%, 16.2%, 18.3%, 13.3%, 10.6%, 10.2%, and 13.0%, for scores of 0 to 6, respectively), it would correspond to a 6.1% absolute improvement in the proportion of patients experiencing a poor outcome (mRS scores 3-6), that is from 47.1% down to 41.0%. This would translate into a 13% relative risk reduction (relative risk of 0.87). Assuming 30% of participating patients will have a stroke mimic and 5% will have missing outcomes, the total sample size is 3116 participants to be recruited over 3 years.

### Recruitment {15}

The study co-investigators, as regional leaders, are responsible for attracting eligible MECs and hospitals from their various networks. High-quality hospitals that have participated in previous studies of The George Institute for Global Health will also been invited to participate. As recruitment occurs in the ambulance, training and screening oversight of the ambulance medical staff is critical to achieving the recruitment target. Regular and specific training on recognition of suspected stroke patients, mastering eligibility criteria, and using the randomization system on smartphone will be provided by RCC staff. All suspected stroke patients are required to be entered into this mini-program, as well as details of the reasons why screen-fail patients are excluded from the trial. A screening report will be given to both the Central Coordinating Center (CCC) and RCC.

## Assignment of intervention: allocation

### Sequence generation {16a}

An internet-based electronic randomization system will be accessed to allocate eligible participants to randomized BP management group in a 1:1 ratio. The randomization sequence will use an algorithm to ensure balance in key prognostic factors, according to the stratification variables of region, age (≥65 vs < 65 years) and FAST score (3-4 vs 2).

### Concealment mechanism {16b}

Concealment of treatment group assignment until the patient has been randomized will be accomplished by making treatment allocation known only after study personnel have enrolled the patient and entered patient characteristics into the internet-based randomization application.

### Implementation {16c}

After patient eligibility is confirmed, the investigator in the ambulance will access a secure 24/7 internet-based electronic randomization system based upon a Wechat app on a mobile phone developed by Bioknow company. Before randomization, the system requires several stratification factors to be entered including region, age, and FAST score. The investigator will then deliver the allocated treatment to the patient according to the randomization result showed on the mobile phone. All suspected acute stroke patients screened for the study that are not included, as well as recruited patients, must be recorded on the screening/enrolment log. This information is to be uploaded to the CCC database.

## Assignment of interventions: blinding

### Who will be blinded {17a}

The treatment is open label to patients and investigators who need to provide BP management in the ambulance and at sites. All other investigators, statisticians and end-point assessors, who are trained to collect outcome measures by face-to-face visit or telephone at 3 months, are blind to the treatment allocation.

### Procedures for unblinding if needed {17b}

Not applicable. This study is an open-label intervention.

## Data collection and management

### Plans for assessment and collection of outcomes {18a}

Ambulance investigators are required to collect eligibility data on patients at the stroke scene or in the ambulance. Measurement, monitoring, and treatment related to BP should be recorded on a specific chart provided by study and then handed over to hospital investigators when bridging occurs at hospital sites.

Hospitals are required to collect data on patients at admission (baseline), 24 h and 7 days BP monitoring chart, separation (day 1; day 7 or at discharge if earlier, transfer from the hospital or death), and all SAEs including death until the 3 months of follow-up. The follow-up assessments are to be undertaken by an investigator who was not involved in the clinical management of the patient, and blind to the study treatment allocation.

Study management will be facilitated by an established internet-based system. Table 1 illustrates the schedule and nature of the data collection required during the study period.

### Plans to promote participant retention and complete follow-up {18b}

The investigators collect a range of contact information, including those of the patient and several relatives and/or friends at hospitalization. The investigators emphasize to participating patients (or their responsible person[s]) during the consent process and at discharge, that they are to receive a telephone call at 3 months to invite them coming back to outpatient to check on their health status face-to-face. If the patients are unable to go to clinic, the assessors will conduct the assessment via telephone directly.

### Data management {19}

Ambulance investigators record the measurement, monitoring, and treatment related to BP on a specific chart provided by study and handed over to hospital investigators when bridging to sites. Hospital investigators are responsible to enter the records into the electronic database. Sites receive paper versions of the CRFs and a procedure manual to serve as a reference guide in using the database; each data element is defined to ensure investigators are accurate and consistent in data entry. All data entry will be completed via a secure web-based electronic data collection system. This will allow for real-time data query generation for values entered outside of pre-set valid ranges, and for consistency checking. This system will speed up data reporting and assist overall trial management for all participating centers. Data entry will be performed at the participating sites. Only authorized staff will have access. All entered data forms will be electronically signed (by use of the unique password) by authorized study staff. All changes made following the initial entry will have an electronically dated audit trail. Centralized coding of outcomes will be performed by a trained medical coder using Medical Dictionary for Regulatory Activities (MedDRA) criteria: he/she will review reporting of outcomes and confirm the accuracy of coding.

### Confidentiality {27}

Every precaution is taken to respect the privacy of participants in the conduct of the study. Only de-identified data will be used for statistical analysis and the publication of results to maintain confidentiality. During monitoring of data quality and adherence to the study protocol, research staff will refer to source documents (medical records) at participating hospitals. This information is included in the PISCF. All individual and site information will be de-identified in reports and results to further protect the confidentiality of participants.

### Plans for collection, laboratory evaluation, and storage of biological specimens for genetic or molecular analysis in this trial/future use {33}

Not applicable. Biological specimens are not collected as part of this study.

## Statistics methods

### Statistical methods for primary and secondary outcomes {20a}

The intention to treat (ITT) principle will be applied in the main analysis, for all participants with presumed acute stroke as if they had received the intervention to which they were supposed to receive, irrespective of whether or not the treatment was actually received, and regardless of subsequent withdrawal from treatment or deviation from the protocol. The primary endpoint of functional recovery at 90 days will be assessed using the mRS score and analyzed using adjusted ordinal logistic regression. The intervention effect will be estimated as the common odds ratio (OR) and its 95% confidence interval (CI). The model will be adjusted by the stratification variables (region, age, and FAST score) as well as pre-morbid mRS score. In case of violation of the proportional odds assumption, the common OR and 95% CI will still be reported; however, a sensitivity analysis will be undertaken using linear regression and treating the mRS score as a continuous variable, thus estimating the effect of the intervention as an adjusted mean difference in mRS score. As a reference, an unadjusted sensitivity analysis without any baseline covariate being included will also be undertaken. The study will use a hierarchical approach for analysis of the study populations, starting with a primary analysis of all participants with a confirmed stroke (ICH or IS) and progressing to a secondary population of all randomized patients (i.e. including ICH, IS, transient ischemic attack, and mimics). A per-protocol (PP) analysis will also be undertaken only for those patients who strictly adhered to all aspects of the protocol. Multiplicity will be controlled by sequential gatekeeping. The primary population will be analyzed first with p threshold of 0.05. If the primary population shows *p* ≤ 0.05 on the primary outcome analysis, then the secondary population will next be analyzed also in a hypothesis-confirming manner with *p* threshold of 0.05. If the primary population shows *p* > 0.05, then the secondary population will next be analyzed in an exploratory manner (with nominal *p* threshold of 0.05). No further adjustment for multiplicity is planned since all secondary analyzes are hypothesis-generating and designed to support the primary analysis.

Binary endpoints such as death and dependency and early neurological deterioration will be analyzed using adjusted binary logistic regression. Continuous outcomes, such as NIHSS score or changes in hematoma volume, will be analyzed using linear regression that includes the baseline outcome value (e.g. NIHSS score or hematoma volume) as a covariate.

A detailed analysis plan including mock tables will be finalized before the database is locked.

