## Trial design {8}

The INTERACT4 study is a multi-center, ambulance-delivered, prospective, randomized controlled, open-label, blinded outcome assessed (PROBE) trial conducted through a network of regional hospital clusters, where a total of 3116 patients with suspected acute stroke are planned to be recruited across 50+ hospitals in China. Potentially eligible patients will be recruited by either of two mechanisms: (i) waiver of consent to the intervention in the ambulance, and written consent for follow-up obtained in hospital; or (ii) consent to the intervention via a brief written consent form in the ambulance, and written consent for follow-up in hospital (if a waiver of consent is not approved by the local ethics committee). Randomized allocation of the intervention will be done in a 1:1 ratio, using a central, automated, mobile-phone accessed mini-program electronic software, with stratification based on region, age (≥ 65 vs < 65 years) and Face/Arm/Speech/Time (FAST) deficit severity score (score 3-4 vs 2). Ambulance staff are trained in the study protocol, covering approaches to assessment, randomization, treatment, and collection of key baseline data. All information in ambulance, including basic demographics, randomized treatment allocation, and BP measurement and treatment details, are collected through the mobile electronic database system which is connected to investigator clinicians at local/regional hospitals. Other relevant documents, such as the consent forms and BP charts, are handed over to hospital investigators as part of the transfer of care process. Endpoint assessments are blinded to treatment allocation. A schema of the study design is provided (Fig. 1).

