#### Intervention description {11a}

The intervention, intensive BP management initiated in the ambulance, is to commence as early as possible after assessment of a patient, and to achieve a systolic BP level < 140 mmHg within 30 min, and to maintain this BP level for the next 7 days, or the time of hospital discharge should this occur earlier.

A recommended treatment regime is giving an IV bolus of 25 mg urapidil administered over 1 min, and another 25 mg urapidil bolus if the BP level persists > 150 mmHg after 5 min. Urapidil is a sympatholytic antihypertensive drug, which acts both as an α_1_-adrenoceptor antagonist and a 5-HT1A receptor agonist, and has a rapid onset (5 min, maximum at 15–30 min) and no effect on intracranial pressure (ICP). BP monitoring in the ambulance will occur every 5 min on electronic charts, delivered to the hospital staff. Allocation to early intensive BP lowering will be notified to hospital investigators as early as possible by the ambulance staff. Patients should keep a horizontal position while being transported to the hospital or other location. IV bolus (or maintenance infusion) treatment with urapidil will continue in the emergency department (ED), where it is anticipated that patients will stay (except for acute CT or MR imaging) until they are clinically stable, and that the target BP is achieved and maintained. BP lowering treatment chosen by the treating clinician will be continued in an acute stroke unit or other monitored facility, to maintain a systolic BP level < 140 mmHg for the next 7 days. Oral BP lowering agents (dependent upon local availability) can be used after a stable target BP level is reached, but it is expected that IV therapy will continue to be required during the initiation of oral antihypertensive therapy, to maintain the systolic BP levels of < 140 mmHg. A systolic BP < 130 mmHg is considered the threshold for cessation of therapy. Each site receives a standardized, stepped titratable, intravenous BP lowering protocol, based upon available medications, that is established in advance.

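### NIHSS and haematoma analyses start from a hospital-admission value taken after ambulance treatment begins, so they estimate only the effect after arrival

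*Protocol article*

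**What the plan says.** All references are to the protocol article.

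- **Model.** Statistical methods {20a} analyses continuous outcomes, naming NIHSS and change in haematoma volume, by "linear regression that includes the baseline outcome value (e.g. NIHSS score or hematoma volume) as a covariate". Outcomes {12} says the same of NIHSS at 24 h and 7 days: "with analysis as a continuous outcome using linear regression with adjustment for baseline score".
- **Haematoma growth.** Outcomes {12} specifies "hematoma volume at presentation and 24 h, with analysis as dichotomized outcomes of relative" and absolute cut-offs (above 33% and above 6 mL), so growth is counted from the presentation scan.
- **When baseline is.** Plans for assessment {18a}: "Hospitals are required to collect data on patients at admission (baseline", followed by the later time points. In Table 1, NIHSS and CT first appear on the Baseline form (B), not on the screening and enrolment form (A).
- **When treatment starts.** Intervention description {11a}: "intensive BP management initiated in the ambulance, is to commence as early as possible after assessment of a patient". Implementation {16c} has the ambulance investigator randomise and then deliver the allocated treatment.
- **What the ambulance records.** Trial design {8}: "All information in ambulance, including basic demographics, randomized treatment allocation, and BP measurement and treatment details". Neither NIHSS nor imaging is named.

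**The concern.** A covariate called baseline is normally a value that treatment cannot have touched. Here both values are taken after randomisation and, in the intensive arm, after treatment is meant to have begun. Each is also an earlier measurement of the outcome itself. Adjusting for it, or counting growth from it, asks what treatment did from hospital arrival onwards, not what ambulance initiation did in total.

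The difference matters in this trial because the interval before arrival is what separates ambulance-initiated from hospital-initiated treatment. The Background {6a} gives reduced haematoma expansion from pre-hospital BP lowering as a reason for the trial, and Objectives {7} makes it a research question. The same Background raises possible early harm, and the adjustment would hide that just as well.

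**Working it through.** **1. The plan's own figure.** The plan gives no number on this point. Its one calculated figure, 3116, uses neither NIHSS nor haematoma volume. Whitehead's formula with the stated mRS distribution, OR 0.78, two-sided 0.05 and 90% power gives 2,096 analysable patients. Dividing by 0.70 × 0.95 gives 3,151, which is 1.1% above 3116. Nothing below changes it.

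**2. Order of events.**

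| Step | Place | Source |
|---|---|---|
| Region, age and FAST score entered; randomisation | Ambulance | Implementation {16c} |
| Intensive treatment starts; drug has "rapid onset (5 min, maximum at 15–30 min") | Ambulance | Intervention description {11a} |
| Controls treated only if BP stays very high | Ambulance | Choice of comparators {6b} |
| Transport, averaging 15 min (Shanghai) and 20 min (Chengdu) | Ambulance | Discussion |
| First NIHSS, first CT | Hospital | {18a}, Table 1, {12} |

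The arms can therefore differ in BP before either value exists.

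**3. What the adjusted model estimates.** For linear regression on treatment and admission value, the standard covariance-analysis identity is

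adjusted effect = D_Y − b × D_X,

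where D_Y is the difference between arms in the 24 h value, D_X the difference at admission, and b the within-arm slope of the 24 h value on the admission value. If a share s of the total effect is already present at admission and carries forward, b × D_X = s × D_Y, so the adjusted effect is (1 − s) × D_Y.

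**4. Numbers for NIHSS (all inputs assumed).** Total effect −1.0 point at 24 h. Pre-treatment severity has mean 12 and SD 7. The admission value is that severity, plus any early effect, plus noise of SD 2. The 24 h value is 2 + 0.9 × admission value, plus the later effect, plus noise of SD 4. Simulation used 400,000 patients per row.

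| Share s at admission | (1 − s) × −1.0 | Simulated, admission-adjusted | Simulated, unadjusted | Simulated, adjusted for true pre-treatment value |
|---|---|---|---|---|
| 0% | −1.00 | −0.99 | −1.03 | −1.00 |
| 10% | −0.90 | −0.90 | −0.99 | −1.00 |
| 25% | −0.75 | −0.75 | −1.00 | −1.01 |
| 50% | −0.50 | −0.52 | −1.01 | −1.01 |
| 75% | −0.25 | −0.22 | −0.96 | −0.98 |
| 100% | 0.00 | 0.00 | −0.99 | −1.00 |

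**5. Direction.** The identity works both ways. Suppose early harm of +0.25 points carries forward and the later effect is −0.75. The total is +0.25 − 0.75 = −0.50, but the admission-adjusted estimate is −0.75, which flatters treatment.

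**6. Haematoma.** Regressing change on treatment and first volume gives the same treatment coefficient as regressing the 24 h volume on them, so a change score does not avoid the problem. An unadjusted change score is the case b = 1. The two growth cut-offs also begin at the first scan. Dropping the covariate alone would therefore not recover a total effect, and no pre-treatment scan is scheduled.

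**7. What dropping the adjustment costs in precision.** In the step 4 model, the unadjusted within-arm variance is 0.81 × (49 + 4) + 16 = 58.93, SD 7.68, against 4 after admission adjustment. The unadjusted standard error is 7.68 / 4 = 1.92 times as large. The adjusted z-statistic relative to the unadjusted one is (1 − s) × 1.92: 1.73 at s = 10%, 1.44 at 25% and 0.96 at 50%. For haematoma volume, illustrative simulations with assumed volume and growth distributions, error-free CT and no other covariates gave ratios of about 1.7 to 2.9 in mL and 2.5 to 4.1 on the log scale, even with half the growth before the scan.

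**8. Primary analysis.** The mRS model in {20a} adjusts for region, age, FAST score and pre-morbid mRS. The first three are entered before randomisation and the fourth describes the state before the stroke. None raises this problem.

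**The case against.** **The share may be small.** Transport averages 15 to 20 min, the drug peaks at 15–30 min, and the outcomes are at 24 h and 7 days. The Discussion also reports intensive-arm patients left untreated in the ambulance. This stands: the loss is conditional, and it is zero if nothing changes before measurement.

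**Baseline may be used loosely.** Trial design {8} has ambulance staff collecting some baseline data. That does not help here, because Table 1 puts NIHSS and CT on form B and {12} takes the first volume at presentation.

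**Growth after arrival is a legitimate quantity, and admission adjustment is efficient.** This also stands. Step 7 shows that replacing the growth analyses with an unconditioned 24 h volume could lose most of the power to detect slower growth.

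**These are secondary outcomes**, which {20a} calls hypothesis-generating. True, and it limits the weight of the point. But the covariate rule is fixed in the protocol, and an analysis plan that followed it would carry it forward.

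A reader might infer three stronger points that the documents do not support:

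- *The analyses are biased towards no effect.* They drop any early effect, and step 5 shows that dropping early harm favours treatment.
- *{12} and {20a} contradict each other on haematoma, one dichotomising and the other using continuous change.* {20a} gives general rules by type of endpoint. The growth cut-offs fall under its binary rule and the volumes under its continuous rule, and both analyses can be done.
- *Admission NIHSS or GCS must be barred from the other treatment-effect models.* No other effect model in the article names them.

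**Conclusion.** The point holds for NIHSS at 24 h and 7 days, for haematoma volume change and for the two growth cut-offs. As specified, these analyses estimate the effect after hospital arrival and exclude any effect before it, whether benefit or harm. The proportion excluded is the share of the effect present at admission. At assumed shares of 10, 25 and 50%, about 0.9, 0.75 and 0.5 of a true 1.0-point NIHSS effect remain.

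The timing rests on the protocol's own statements. The size rests on an unknown share and on early differences carrying forward along the within-arm slope. I put no mL figure on the haematoma loss, because it would depend wholly on assumed volume and growth distributions. The primary result and the sample size are untouched. The change is worth making because it costs little and bears on a stated reason for the trial.

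**What to change.** In Outcomes {12} and Statistical methods {20a}, and in the analysis plan that follows them:

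1. Stop describing admission NIHSS and first-CT volume as pre-treatment baseline values.
2. For NIHSS at 24 h and 7 days, and for (log) haematoma volume at 24 h, add analyses adjusted only for variables fixed before randomisation: region, age, FAST score and ambulance systolic BP. The first three are entered at randomisation, and systolic BP is recorded twice for eligibility. Base any claim about the total effect of ambulance-initiated treatment on these analyses.
3. Report admission NIHSS and first-CT volume by arm, as outcomes.
4. Keep the admission-adjusted models and the growth cut-offs from the first CT, labelled as effects after hospital arrival.

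**Cost.** Wording and a few more analyses, with no new data. The added estimates are markedly less precise, especially for haematoma volume, which is why they are added and do not replace the growth analyses.
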